### Study design

3.1

The study is a confirmatory, randomized controlled trial with two arms that takes place in a monocentric, national setting and assesses effectiveness.

To evaluate feasibility, qualitative semi-structured interviews will be conducted with specialists working with refugees prior to the intervention study. These interviews will follow an inductive and explorative approach and involve staff from institutions such as asylum centers and dormitories for unaccompanied minors. To estimate the feasibility and effectiveness of this trial, specialists will be interviewed about their daily challenges, language and cultural barriers, as well as potential difficulties with the implementation and adaptation of START NOW. The inclusion of qualitative information can help to better understand how a complex intervention such as START NOW can work and aid in the adaptation process of the intervention (31).

After the conduction of these interviews, possible participants taking part in the intervention study are screened for eligibility. For those who are eligible, the study duration will be 6 months, including three assessments (shown in Figure 1): a baseline assessment (t1), a post-treatment assessment (t2), and a 12-weeks follow-up assessment (t3). In case a participant has missed a session, they will be marked as absent and the number of sessions will be taken into consideration in the data analysis. To minimize bias, participants will be randomly assigned to one of two experimental group conditions, (1) group skills training using an adapted version of START NOW, (2) TAU. Randomization should take place within 2 weeks before the intervention, after the baseline assessment (t1) has been conducted. Between t1 and t2, the intervention phase takes place over a period of 10 weeks, with one session per week for each group. The study takes place in a group setting since conducting mental health interventions via group workshops, which aim to enhance social interaction was observed to have a positive impact on participants’ mental health (19). For ethical reasons and to increase study-related commitment, participants in the control group (receiving TAU) as well as non-eligible participants will be offered the chance to receive treatment after the study concludes.

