#### Screening measures

3.5.1

Screening measures include demographics such as age or country of origin, inclusion criteria including the HSCL-25 and the K10, exclusion criteria including the SBQ-R, and the World Health Organization Well-Being Index (WHO-5).

The K10 is a 10-item self-report questionnaire aimed at assessing overall distress levels. It gathers information on anxiety and depressive symptoms experienced by an individual within the past 4 weeks. Participants answer on a 5-point Likert Scale (1 = none of the time, 5 = all of the time), with scores ranging from 10 to 50. Higher scores indicate a higher possibility that participants suffer from a mental disorder.

The SBQ-R is a brief, 4-item self-report measure of past suicidal behavior. The questionnaire is used with adolescents between the ages of 13 and 18. Each question is rated on its own scale, with specific point values assigned to the answers and the total score ranging from 3 to 18 points. A higher score indicates a greater likelihood of engaging in suicidal behavior.

The WHO-5 is a brief self-report assessment used to measure mental well-being during the past 2 weeks. It includes five items with positive wording, each rated on a 6-point Likert scale (0 = at no time, 5 = all of the time). The total raw score, which ranges from 0 to 25, is multiplied by 4 to generate the final score. A high score indicates a higher level of well-being.

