#### Primary outcome

3.5.2

The primary outcome, symptoms of depression and anxiety, will be measured by the HSCL-25 (36) at baseline (t1), at the end of the intervention (t2) and 12 weeks after the end of the intervention (t3) to determine the effectiveness of the intervention. The HSCL-25 is a 25-item self-report questionnaire, on which participants rate if physical, emotional, or psychological symptoms indicating depression, anxiety, and trauma have affected them over the past week. Answers are given on a 4-point Likert Scale (1 = not at all; 4 = extremely), and total scores can range from 25 to 100, with higher scores indicating greater levels of depression, anxiety and trauma, respectively.

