### Sample size

4.1

The sample size is estimated based on a power analysis for repeated measures ANOVA including within-between interaction with 3 measuring time-points (t1, t2 and t3) and 2*2 groups (intervention vs. TAU, female vs. male). Standard parameters are set at alpha = 0.05, power = 0.95, and a clinically meaningful medium effect size *f* = 0.25. Considering an attrition rate of 30% (59), the total number of participants should be 80, with approximately 40 participants in the treatment (treatment groups of 5 to 10 participants each) and 40 participants in the control group.

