### Statistical analyses

4.2

For statistical analyses, we will use R with its graphical user interface R Studio. The significance level will be 0.05 for all analyses. An effect of at least moderate size will be considered as clinically relevant. To test our hypotheses, we will use multilevel models with primary and secondary outcome measures as dependent variables (three individual models for depression, perceived stress, and emotion recognition), and with timepoint (baseline, post-treatment, follow-up) and intervention condition (START NOW vs. TAU) including their interaction as independent variables. A significant interaction between intervention condition and time suggests a difference in symptom change depending on treatment group. In case of significant main or interaction effects, we will evaluate post-hoc contrast considering time and intervention condition. Treatment group will be added as level two in the multilevel framework.

Using multilevel models will allow to analyze data on the observational level, which provides more information in contrast to calculating change scores or using repeated measures ANOVA, increasing measurement accuracy and power. In addition, multilevel mixed models can handle missing observations and allow to examine random effects at the intercept and slope level. Furthermore, we will test model improvement when considering quadratic versus linear trends for time, random effects for time, and correlation structure between timepoints. Covariates, including participant age, gender, and post-migration stress will be added if they differ between intervention groups. On group level, possible covariates include facilitator, institution or cultural background.

To analyze perceived stress and resilience as potential mechanisms in treatment success, we will use bias-corrected bootstrap mediation models with intervention condition as predictor, change in symptoms of depression as outcome, and change in stress/resilience as mediator. Change in symptoms of depression and indicators of stress/resilience will consist of participant’s random slope for time extracted from the multilevel mixed models depending on results of the first hypothesis.

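### Two HSCL-25 scores precede randomisation, but the primary model uses neither for planned adjustment: t1 stays an outcome level and t0 has no role, at a cost in precision

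*Protocol article*

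**What the plan says.** - Table 1 (section 3.5) marks the HSCL-25 at t0, t1, t2 and t3. The only use stated for the t0 score is eligibility: section 3.5.1 lists among the screening measures the "inclusion criteria including the HSCL-25 and the K10". Section 3.3 admits a participant with HSCL-25 above 1.75 or K10 above 20.
- Section 3.1 fixes the order: "Randomization should take place within 2 weeks before the intervention, after the baseline assessment (t1) has been conducted". Both t0 and t1 therefore precede allocation.
- Section 3.5.2 defines the primary outcome at t1, t2 and t3, and section 4.1 counts the same three times.
- Section 4.2 specifies multilevel models "with timepoint (baseline, post-treatment, follow-up) and intervention condition (START NOW vs. TAU) including their interaction as independent variables". Baseline is thus a level of the time factor, on the outcome side.
- On adjustment, section 4.2 says: "Covariates, including participant age, gender, and post-migration stress will be added if they differ between intervention groups". Neither HSCL-25 pre-randomisation score is named there.

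**The concern.** In a randomised trial the reason to adjust for a baseline variable is that it predicts the outcome, not that the arms happen to differ on it. An earlier score on the primary outcome is normally among the strongest predictors available, and this trial has two. With t1 as an outcome level and free arm means at every time, the condition-by-time contrast at t2 compares the arms on t2 minus t1. Such a contrast carries the full noise of t1, whereas a covariate is weighted by how well it predicts. The t0 score is not used at all.

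What is at stake is the width of the confidence interval for START NOW Adapted versus TAU. The plan expects 30% attrition from 80, so 80 × 0.7 = 56 completers, in a population that is hard to recruit. The data that would narrow the interval are already being collected.

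**Working it through.** **The plan's own figure.** Section 4.1 gives "Standard parameters are set at alpha = 0.05, power = 0.95", f = 0.25, three times and 2 × 2 = 4 groups. For the within-between interaction, λ = f²·N·m/(1−ρ), with m = 3 times, k = 4 groups, df1 = (k−1)(m−1) and df2 = (N−k)(m−1). The article gives neither ρ nor a sphericity correction. Assuming ρ = 0.5 and none, N = 59, or 60 when balanced. Then 60 × 1.3 = 78, close to the stated 80. With 56 completers the same formula gives power 0.937. The t0 score plays no part in this calculation.

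**Variance factors for the t2 contrast.** Outcome SD is 1, ρ is the correlation of t2 with each pre-randomisation score, and r01 is the correlation of t0 with t1:
- model as written (change from t1): 2(1−ρ)
- t1 as covariate: 1−ρ²
- t1 and t0 as covariates: 1−2ρ²/(1+r01)

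With all correlations equal and no selection at entry:

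| ρ | as written | t1 | t1 + t0 | cut by t1 + t0 against as written |
|---|---|---|---|---|
| 0.5 | 1.000 | 0.750 | 0.667 | 33% |
| 0.6 | 0.800 | 0.640 | 0.550 | 31% |
| 0.7 | 0.600 | 0.510 | 0.424 | 29% |

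For an assumed difference of 0.5 SD and 28 completers per arm, power across the three columns is 0.464, 0.579 and 0.630 at ρ = 0.5; 0.552, 0.647 and 0.713 at 0.6; 0.676, 0.745 and 0.820 at 0.7.

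**Entry rule applied.** Entry selects on t0, so the gain from t0 was simulated among those meeting HSCL-25 > 1.75 or K10 > 20. Means, SDs and the K10 correlation were assumed, and about 74% were eligible. The table gives the residual variance of t2 given t1 and t0, relative to t1 alone:

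| correlations t0–t1 / t1–t2 / t0–t2 | ratio | further cut from t0 |
|---|---|---|
| .5/.5/.5 | 0.920 | 8% |
| .6/.6/.6 | 0.893 | 11% |
| .7/.7/.7 | 0.863 | 14% |
| .7/.5/.5 | 0.953 | 5% |
| .8/.6/.6 | 0.947 | 5% |
| .8/.5/.5 | 0.969 | 3% |
| .8/.6/.55 | 0.982 | 2% |
| .75/.5/.45 | 0.986 | 1% |

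A second simulation of seven of these patterns (all but .8/.5/.5) agreed within 0.002. Against the model as written, t1 and t0 together cut the variance by 19–33% across those seven.

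**Shares of t1 and t0.** With equal correlations, selection on t0 leaves the as-written and t1 + t0 factors unchanged, so the t1-only factor is the t1 + t0 factor divided by the ratio above:
- 0.5: 0.667/0.920 = 0.725, so t1 alone cuts 1 − 0.725/1.000 = 27.5% of the 33%
- 0.6: 0.550/0.893 = 0.616, so 1 − 0.616/0.800 = 23% of the 31%
- 0.7: 0.424/0.863 = 0.491, so 1 − 0.491/0.600 = 18% of the 29%

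**Standard errors, 56 completers.** At .6/.6/.6 the mean SE is 0.238 as written, 0.210 with t1 and 0.200 with both. At .8/.6/.55 it is 0.215 with t1 and 0.215 with both; at .75/.5/.45, 0.232 and 0.233. In those two patterns the lost degree of freedom cancels what t0 adds.

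**Adding t0 to the model as written.** The covariance of t0 with t2 − t1 is r02 − r01, where r02 is the t0–t2 correlation. It is zero when the correlations are equal, so t0 cannot help. A mixed-model simulation at 0.6 without selection gave SE 0.238 as written, 0.238 with t0 as a main effect and 0.240 with t0 crossed with time. Over the patterns with the entry rule applied, the variance changes by 0–6%.

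**The case against.** A screening score for eligibility and a later score as baseline is ordinary practice, and nothing in the article is contradictory. The word including leaves the covariate list open, and an analysis plan that is not shown may name baseline HSCL-25. That stands for the list. It does not remove the two stated choices: baseline is a level of the time factor, and adjustment depends on observed differences between arms.

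The upper figures for t0 need t0 to predict t2 as well as t1 does. The t1 score is nearer in time, so the patterns with a 1–2% gain are at least as plausible. The interval between t0 and t1 is not given. This objection stands and is why a range is reported.

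Three stronger readings are tempting, and the documents do not support them:
- A reader might infer that the unused t0 score is the main loss and that one added line recovers it. The larger loss is the place of t1 in the model, and adding t0 alone gains little or nothing.
- A reader might infer bias. Both scores precede randomisation, and the estimates were unbiased in every simulated pattern.
- A reader might infer that conditioning on t0 deals with selection at entry. Selection precedes allocation, so it does not bias the contrast. Entry is by HSCL-25 or K10, so t0 HSCL-25 does not fully capture the rule.

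**Conclusion.** The point holds as a modest, optional gain in precision. The HSCL-25 model as written estimates what is in effect a change from t1 and plans no adjustment for either pre-randomisation score. Using both as covariates would cut the variance of the t2 contrast by about 19–33%, most of it from t1. Taken alone, the t0 share of 1–14% is worth about 1 to 9 completers: 56/0.986 = 56.8 and 56/0.863 = 64.9. After the lost degree of freedom it is about nil if t0 is clearly less predictive.

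The sizes rest on assumed correlations, means and SDs, on time treated as three categories, and on complete t1 and t2 scores. They ignore clustering within treatment groups.

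**What to change.** In section 4.2, prespecify for the HSCL-25 a model with t2 and t3 as outcomes, condition, time and their interaction, and t1 and t0 HSCL-25 as covariates, each crossed with time, for every participant whatever the observed balance. An alternative keeps t1 as an outcome level but constrains the arm means to be equal there, with t0 as a covariate. Because entry selects on t0, it is better used as a covariate than as an outcome row.

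The cost is a restructured model, not one extra term. Two covariates crossed with two post-randomisation times use up to four coefficients. Participants with neither t2 nor t3 contribute nothing to the first model; under the constrained alternative their t1 scores stay in. No new data are needed, and the sample size need not change.

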### Hypotheses

2.2

Based on our primary and secondary endpoints, we have formulated the following hypotheses.

START NOW Adapted will be more effective than TAU in reducing symptoms of depression and anxiety, as assessed by the Hopkins Symptom Checklist (HSCL-25).START NOW Adapted will be more effective than TAU in reducing perceived stress, as assessed by the Perceived Stress Scale (PSS-10).START NOW Adapted will be more effective than TAU in increasing social-ecological resilience, as assessed by the Child and Youth Resilience Measure (CYRM-R).START NOW Adapted will be more effective than TAU in increasing facial emotion recognition, as assessed by the Penn Emotion Recognition Task (ER-40).

Additionally, besides investigating the intervention’s effectiveness, we aim to examine potential mediators to uncover the mechanisms of action (28). Specifically, we hypothesize:

The relationship between the group condition and changes in depressive and anxious symptoms (HSCL-25) is mediated by stress reduction (PSS-10).The relationship between the group condition and changes in depressive and anxious symptoms (HSCL-25) is mediated by increased resilience (CYRM-R).The relationship between increased resilience (CYRM-R) and changes in depressive and anxious symptoms (HSCL-25) is mediated by stress reduction (PSS-10).

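### Mediation is tested on random slopes that already have the treatment effect removed, so both condition-to-symptom mediation hypotheses must come out null

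*Protocol article*

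**What the plan says.** Section 2.2 of the protocol article (Hypotheses) sets out three mediation hypotheses. Two start from randomised condition: "The relationship between the group condition and changes in depressive and anxious symptoms (HSCL-25) is mediated by stress reduction (PSS-10"), and a parallel one in which the effect of condition on "changes in depressive and anxious symptoms (HSCL-25) is mediated by increased resilience (CYRM-R"). The third runs from resilience through stress to symptoms.

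Section 4.2 (Statistical analyses) says how they will be tested. The multilevel models have "timepoint (baseline, post-treatment, follow-up) and intervention condition (START NOW vs. TAU) including their interaction as independent variables". The mediation step uses "bias-corrected bootstrap mediation models with intervention condition as predictor, change in symptoms of depression as outcome, and change in stress/resilience as mediator". Both change variables are then defined as the participant's "random slope for time extracted from the multilevel mixed models depending on results of the first hypothesis". No other model is described from which slopes could be taken.

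**The concern.** In these models the effect of condition on change sits in the fixed interaction term, and Section 4.2 itself reads that term as the between-arm difference in symptom change. The random slope is what is left for each participant after their arm's mean slope has been taken out. Using it as the mediator asks condition to predict a quantity from which condition has already been removed.

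Two of the three mediation hypotheses would then return a null whether or not they are true. The trial is described as confirmatory (Section 3.1), and these hypotheses are meant to show how the intervention works. A null could be published as evidence that neither stress nor resilience is a mechanism of action.

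A lesser point is that one slope over t1 to t3 gives mediator and outcome the same time window. The mediator's change does not precede the outcome's, although t2 and t3 are both measured.

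**Working it through.** The plan gives no figure for this analysis, so there is none to reproduce. The check is algebra, followed by simulation.

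**Inputs from the protocol article**
- Fixed part: timepoint, condition and their interaction (4.2).
- Mediator and outcome in the mediation: random slope for time (4.2).
- 80 participants, about 40 per arm; three timepoints; 30% attrition (4.1).
- Significance level 0.05 (4.2). A 95% bootstrap interval is assumed, since sidedness is not stated.

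**Algebra**
1. Write the model for participant *i* as y_i = X_i β + Z_i u_i + e_i, with Z_i = (1, time), V_i = Z_i G Z_i' + σ²I and residual r_i = y_i − X_i β̂.
2. The fixed effects solve Σ X_i' V_i⁻¹ r_i = 0.
3. The predicted random effects are û_i = G Z_i' V_i⁻¹ r_i.
4. X_i contains Z_i and condition × Z_i. Step 2 therefore forces Σ Z_i' V_i⁻¹ r_i = 0 separately within each arm.
5. Hence Σ û_i = G × 0 = 0 within each arm, for the intercept and for the slope.
6. With M the mediator slope and Y the outcome slope:
   - path a (condition to M) = mean û(M) under START NOW − mean û(M) under TAU = 0 − 0 = 0
   - total effect of condition on Y = 0 − 0 = 0
   - indirect effect = a × b = 0 × b = 0

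Nothing here requires complete data. The result also holds with time as a factor, added covariates or a therapy-group random effect.

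**Simulation**

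There were 60 trials of 80 participants with three visits and 30% dropout. Assumed values, not taken from the documents: effect of condition on the mediator slope −0.5; effect of the mediator slope on the outcome slope 0.7; so the true indirect effect is −0.5 × 0.7 = −0.35. Models were REML fits with random intercept and slope, followed by a 95% bias-corrected bootstrap with 1,000 draws.

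| Slope used in the mediation | Mean a | Mean indirect effect | Mediation detected |
|---|---|---|---|
| Random slope, interaction in the model (as written) | 0 (largest absolute value 7e-16) | −2e-17 | 0/60 |
| Random slope, interaction left out | −0.321 | −0.165 | 55/60 |
| Total slope (time + interaction + random deviation) | −0.494 | −0.259 | 60/60 |

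In the first row path b averaged 0.53, so the mediator-to-outcome association was visible and only the path from condition was lost.

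A separate set of 60 simulated trials (40 per arm, full mediation, assumed effect −0.50 on the mediator slope) gave the same picture. The fixed interaction averaged about −0.48 while the arm difference in extracted slopes was at most 6e-16. Observed change scores (t1 to t2 for the mediator, t1 to t3 for the outcome) gave a of about −0.50 and an indirect effect of about −0.20.

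**The case against.** The strongest reply is that the article does not fully specify the extraction. The clause about the first hypothesis, at the end of the defining sentence, could mean that the extraction model changes with that result. The authors might also mean the participant's total slope. On either reading path a is not forced to zero, as the table shows. An unseen analysis plan might settle this.

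The clause is indeed unclear, but it names no other model. If it means dropping the interaction when it is not significant, the zero still applies whenever the interaction is kept, which is when mechanism matters most. Adding back only the common time coefficient shifts both arms equally and leaves the zero in place.

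Reading the text as total slopes is not a safe repair. Each slope is shrunk towards its arm's mean, so the spread within arms is understated while the arm difference is kept in full. In a simulation with no true effect of condition on the mediator, this approach rejected in about 55% of runs at a nominal 5%. The exact rate depends on the assumed variances, but the direction does not. The 60/60 in the table should therefore not be read as valid power.

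Four limits stand:
- The third hypothesis does not start from condition and is not zeroed.
- Section 4.2 lists no multilevel model for CYRM-R, so that the resilience slopes come from a model with the interaction is inferred.
- The time-window point limits causal reading but contradicts nothing in the hypotheses, which speak of change mediated by change.
- Mediation is additional to the effectiveness question, and an effect of order 1e-16 beside a significant interaction might be noticed and corrected from the same data.

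**Conclusion.** The concern holds. Followed as written, the analysis gives an estimated condition-to-mediator path, total effect and indirect effect of exactly zero for both hypotheses that start from condition. This is a wrong specification, not a detail left out of a condensed article.

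The conclusion rests on taking a random slope in its usual sense, as the deviation from the fixed part, and on the interaction being in the model from which it is extracted. The exact zero needs no assumed effect size or variance. The other simulated estimates and detection rates do, and they say nothing about the effects this trial will find. The primary and secondary treatment comparisons, the randomisation and the sample size are not affected. The paragraph must be corrected before the mediation analysis is run.

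**What to change.** Do not use extracted random slopes as mediator or outcome. Replace the definition in Section 4.2 with one of these:

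1. Regress the mediator at t2 (PSS-10 or CYRM-R) on condition and the baseline mediator. Regress HSCL-25 at t3 on condition, the t2 mediator, the baseline mediator and baseline HSCL-25. Bootstrap the product of the condition-to-mediator and mediator-to-outcome coefficients. This also puts the mediator before the outcome. The outcome becomes the baseline-adjusted t3 level, so the text should say so and state how missing t2 and t3 values are handled, given the expected 30% attrition.
2. Fit a latent-growth or multilevel structural equation model in which condition predicts the slopes and the indirect effect is estimated within the one model. This keeps change as the quantity of interest and uses all available visits.

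In the same edit, name a model for CYRM-R, use the HSCL-25 total as Section 2.2 does (Section 4.2 speaks of depression only), and remove or explain the clause that makes the definition depend on the first hypothesis. Random effects for time are kept only if they improve the model, so under the present text the slopes might not exist at all; either option removes that dependence on the outcome of model selection.

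The cost is one reworded paragraph and different R code. No new data, visits or participants are needed.

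### Mediation variables taken as random slopes from models that already hold condition-by-time carry no arm effect, so the two mediation hypotheses with condition as predictor cannot be supported as written

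*Protocol article*

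**What the plan says.** Section 4.2 (Statistical analyses) gives the multilevel models timepoint and "intervention condition (START NOW vs. TAU) including their interaction as independent variables". It reads the treatment effect from that interaction: "A significant interaction between intervention condition and time suggests a difference in symptom change depending on treatment group".

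For mechanisms, the same section plans "bias-corrected bootstrap mediation models with intervention condition as predictor, change in symptoms of depression as outcome, and change in stress/resilience as mediator". Both change variables are defined as the participant's "random slope for time extracted from the multilevel mixed models". A closing clause ties this to what the test of the first hypothesis shows, and is not explained.

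Whether the models contain a random slope at all is left to a test: "we will test model improvement when considering quadratic versus linear trends for time, random effects for time". The models are listed as "three individual models for depression, perceived stress, and emotion recognition", so no source model is named for a resilience slope.

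Section 2.2 (Hypotheses) has three mediation hypotheses. Two start from group condition, with stress (PSS-10) or resilience (CYRM-R) as mediator of change in HSCL-25. The third runs from resilience through stress to symptoms and does not start from condition.

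**The concern.** Mediation by stress or resilience needs the arms to differ in how the mediator changes. The variable chosen to represent change has had that difference removed, because the model has already assigned it to the fixed condition-by-time term. Regressing the variable on condition then returns nothing, whatever START NOW Adapted does.

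At stake is the interpretation of a negative result. The trial could report that neither stress reduction nor resilience carries the effect, when the result follows from how the variables were built and says nothing about mechanism.

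**Working it through.** **Inputs from the article.** Fixed part: time, condition, condition × time (Section 4.2). Mediation predictor: condition (4.2). Mediator and outcome: extracted random slopes (4.2). Total N = 80 with 30% attrition (4.1), which leaves 80 × 0.70 = 56 completers. The article gives no effect size for mediation, so there is no planned figure to reproduce.

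**Step 1: where the arm effect sits.** With A = 1 for START NOW Adapted and 0 for TAU, write the model for participant *i* at time *t* as

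y = β0 + β1·t + β2·A + β3·t·A + u0i + u1i·t + e.

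The participant's full slope is β1 + β3·A + u1i. The arms differ by β3. The extracted random slope is the prediction of u1i alone.

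**Step 2: the arm means of the extracted slopes.** The predictions are û_i = D Z_i′[V⁻¹(y − Xβ̂)]_i, and the estimates satisfy X′V⁻¹(y − Xβ̂) = 0. X contains an intercept and a time slope for each arm, so within an arm the columns of Z lie in the span of X. Hence the sum of Z_i′[V⁻¹(y − Xβ̂)]_i over each arm is 0, and so is the sum of û_i. Therefore:

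- condition-to-mediator path: a = 0 − 0 = 0;
- total effect of condition on the symptom slope: c = 0 − 0 = 0;
- indirect effect: a × b = 0 × b = 0.

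The argument holds for any V, so dropout, a treatment-group level or added covariates do not change it. It also holds for categorical time, because linear time lies in the span of the visit indicators. In R, a coefficient extraction that adds the common slope β1 to each û leaves the difference at (β1 + 0) − (β1 + 0) = 0.

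**Step 3: numerical check.** Assumed for illustration: true arm effect on the mediator slope −0.4, true b path 0.8, N = 80, 30% dropout, REML, bias-corrected bootstrap.

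| Variable used as change | Runs | Path a | Mediation detected |
|---|---|---|---|
| Random slope, condition × time in model, linear time | 150 | largest absolute value 8.7e-16 | 0% |
| Same, categorical time | 40 | largest absolute value 8.2e-16 | 0% |
| Same, added covariate | 40 | largest absolute value 6.1e-16 | 0% |
| Same, mediation limited to those with at least 2 visits | 150 | mean 0.000, largest absolute value 0.034 | 0% |
| Random slope, model without condition × time | 150 | mean −0.23 | 91–93% |
| Fixed part including condition × time, plus random slope | 150 | mean −0.407 | 98% |

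A further 200 runs at N = 80 added a treatment-group level and an age covariate. The mean fixed interaction was −0.80 (true value −0.80), and the largest arm difference in random slopes was 8.7e-16.

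**Step 4: the last row is not a remedy.** Predicted deviations are shrunken, so their spread within an arm is too small, while the interaction added back keeps its full sampling error. With no true arm effect, a nominal 5% test of the condition-to-mediator path on such slopes rejected in 61% of simulated runs. The rate depends on the assumed variances. A check with 200 runs per setting, N = 80 and 30% dropout gave 27.5% (slope SD 0.4, residual SD 0.4), 50% (0.3, 0.5) and 68.5% (0.2, 0.5). The 98% in the table is therefore not usable power.

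**The case against.** **The text may mean something else.** The authors might intend full participant slopes, or slopes from a model without the interaction, and the clause on the first hypothesis could leave room for that. Under either reading the path is not zero, as the last two table rows show. This much stands: the conclusion depends on the literal wording. But that wording says random slope, and no model without the interaction is described anywhere. If the clause means that mediation follows a significant interaction, the interaction is in the source model exactly when there is an effect to mediate.

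**A fuller document may settle it.** The article condenses a longer plan. Yet this is a stated definition that gives the wrong quantity, which differs from a detail left out.

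**Stronger readings.** A reader might infer that this trial can find no mediation at all. The article does not support that, because the third hypothesis does not use the condition path. A reader might also infer that the path is exactly zero in every analysis. It is so only when the mediation sample matches the model sample; otherwise it is centred on zero. Nor can one say that the random slope will probably be dropped. Testing it means it may be unavailable, but any probability would rest on correlations that the article does not give.

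**Importance.** Section 2.2 introduces mediation as an addition to the question of effectiveness. That objection stands, and it limits the severity.

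**Conclusion.** The point holds for the literal definition in Section 4.2. The two mediation hypotheses with condition as predictor cannot be supported even if true: the condition-to-mediator path and the total effect on symptoms are zero by algebra, or centred on zero when the samples differ. The algebra needs no assumed values. The detection rates in the table do rest on assumed effects and only illustrate it.

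The resilience-to-stress-to-symptoms hypothesis, the primary condition-by-time test, the sample size and the data collection are not affected. Two remarks are minor: the random slope is subject to a model-improvement test and may not be available, and no source model is named for the resilience slope. This should be fixed before analysis, but it does not threaten the main result.

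**What to change.** Replace the extracted random slopes in the mediation paragraph of Section 4.2 by one of the following:

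- **(a)** observed mediator and HSCL-25 scores at named visits, each adjusted for its t1 value, with condition as predictor; or
- **(b)** a joint growth model for mediator and HSCL-25 in which condition predicts the slope factors and the mediator slope predicts the symptom slope, provided it can be estimated with three visits and about 56 to 80 participants.

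For either option, name the resilience (CYRM-R) data or model to be used, and do not let the mediation variable depend on the outcome of a model-improvement test. Do not simply add the fixed interaction back to the shrunken slopes.

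The cost is a rewritten paragraph and no new data. Option (a) is noisier than model-based slopes and needs a stated missing-data method. Option (b) may not converge at this size, so (a) should be named as the fallback.
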